#### 7.3.1 Context and rationale for definition of time 0 (and other primary time anchors) for entry to the study population

Time 0 will be the day of initiation of Drug A/B combination therapy. Only patients who initiate Drug A and B on the same day will be included. A washout covering all available data will be applied to ensure that there is no prior use of either Drug A or Drug B by themselves or in combination prior to time 0.

#### Table 3 Operational Definition of Time 0 (index date) and other primary time anchors

| **Study population name(s)** | **Time Anchor Description**  **(e.g. time 0)** | **Number of entries** | **Type of entry** | **Washout window** | **Care Setting^1^** | **Code Type^2^** | **Diagnosis position** | **Incident with respect to…** | **Measurement characteristics/**  **validation** | **Source of algorithm** |
| --- | --- | --- | --- | --- | --- | --- | --- | --- | --- | --- |
| **Exposure**  Drug A/B | Date of incident dispensation of Drug A/B (time 0) | Single | Incident | [-∞, 0] | n/a | ATCC | n/a | Drug A or Drug B alone, Drug A/B in combination, Drug D | No validation study | Investigator review of drug codes  XYZ registry dispensing data years 2021-2022 |
| **Comparator 1**  (concurrent)  Standard of Care (SoC).  Drug C or Drug D | Date of incident dispensation of standard care  (time 0) | Single | Incident | [-∞, 0] | n/a | ATCC | n/a | Drug C initiators must be incident with respect to Drug A, B, C and D  Drug D initiators must be incident with respect to Drug A, B, D but not C. | No validation study | Investigator review of drug codes  XYZ registry dispensing data years 2021-2022 |
| **Comparator 2**  (historical)  Standard of Care (SoC).  Drug C or Drug D | Date of incident dispensation of standard care (time 0) | Single | Incident | [-∞, 0] | n/a | ATCC | n/a | Drug C initiators must be incident with respect to Drug A, B, C and D  Drug D initiators must be incident with respect to Drug A, B, D but not C. | No validation study | Investigator review of drug codes  XYZ registry dispensing data years 2019-2020 |

^1^ IP = inpatient, OP = outpatient, ED = emergency department, OT = other, n/a = not applicable

^2^See appendix for listing of clinical codes for each study parameter

#### 7.3.2 Context and rationale for study inclusion criteria:

We included patients 18 or older with metastatic [organ] cancer who were biomarker Y+ and progressed within 2 years after 1^st^ line therapy.

#### 7.3.3 Context and rationale for study exclusion criteria

We exclude patients with missing/unknown age or sex. Other exclusion criteria are to be discussed.

#### Table 5. Operational Definitions of Exclusion Criteria

| **Criterion** | **Details** | **Order of application** | **Assessment window** | **Care Settings¹** | **Code Type^2^** | **Diagnosis position^3^** | **Applied to study populations:** | **Measurement characteristics/**  **validation** | **Source for algorithm** |
| --- | --- | --- | --- | --- | --- | --- | --- | --- | --- |
| Age missing |  | Before selection of index date | [0, 0] | n/a | n/a | n/a | Exposure  Comparator 1 Comparator 2 |  | n/a |
| Sex missing/unknown |  | Before selection of index date | [0, 0] | n/a | n/a | n/a | Exposure  Comparator 1 Comparator 2 |  | n/a |
| To be discussed |  | Before selection of index date | *To be discussed* | *n/a* | *n/a* | *n/a* | Exposure  Comparator 1 Comparator 2 |  | *n/a* |

^1^ IP = inpatient, OP = outpatient, ED = emergency department, OT = other, n/a = not applicable

^2^ See appendix for listing of clinical codes for each study parameter

^3^ Specify whether a diagnosis code is required to be in the primary position (main reason for encounter)

- 1. Variables

#### 7.4.1 Context and rationale for exposure(s) of interest

Exposure to Drug A/B and standard of care comparators will be defined using ATCC codes. Drug A/B combination is approved for 2^nd^ or 3^rd^ line therapy for metastatic [organ] cancer for biomarker Y+ cancers. Drugs C and D are approved as standard of care for 2^nd^ and 3^rd^ line therapies, respectively.

**Algorithm to define duration of exposure effect:**

If a refill occurs before the end of days supply dispensed, add overlapping days to the end of the subsequent dispensing’s day supply. Assume that the effect of a pill lasts for 30 days. Therefore, we allow up to a 30 day gap between a dispensation + days supply and refill. We also add 30 days to the last dispensation + days supply in a treatment episode and consider this “exposed” time.

#### Table 6. Operational Definitions of Exposure

| **Exposure group name(s)** | **Detail** | **Washout window** | **Assessment Window** | **Care Setting^1^** | **Code Type^2^** | **Diagnosis position^3^** | **Applied to study populations:** | **Incident with respect to…** | **Measurement characteristics/**  **validation** | **Source of algorithm** |
| --- | --- | --- | --- | --- | --- | --- | --- | --- | --- | --- |
| Exposure: Drug A/B |  | [-∞, 0] | [1, censor] | Hospital | ATCC | n/a | Exposure  Comparator 1 Comparator 2 | Drug A or Drug B alone, Drug A/B in combination, Drug D | No validation study | Investigator review of drug codes  XYZ registry dispensing data years 2021-2022 |
| Comparator 1: SoC  (concurrent) |  | [-∞, 0] | [1, censor] | Hospital, palliative care | ATCC | n/a | Exposure  Comparator 1 Comparator 2 | Drug C initiators must be incident with respect to Drug A, B, C and D  Drug D initiators must be incident with respect to Drug A, B, D but not C. | No validation study | Investigator review of drug codes  XYZ registry dispensing data years 2021-2022 |
| Comparator 2: SoC  (historical) |  | [-∞, 0] | [1, censor] | Hospital, palliative care | ATCC | n/a | Exposure  Comparator 1 Comparator 2 | Drug C initiators must be incident with respect to Drug A, B, C and D  Drug D initiators must be incident with respect to Drug A, B, D but not C. | No validation study | Investigator review of drug codes  XYZ registry dispensing data years 2019-2020 |

^1^ IP = inpatient, OP = outpatient, ED = emergency department, OT = other, n/a = not applicable

^2^ See appendix for listing of clinical codes for each study parameter

^3^ Specify whether a diagnosis code is required to be in the primary position (main reason for encounter)

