#### Table 2 Primary and secondary objectives and research questions

1. **Primary objective and research question**

| **Objective:** | To compare overall survival (OS) in patients > 18 years with metastatic [organ]carcinoma with a biomarker Y+ mutation who have shown progression after first line treatment and have indicated informed consent for longitudinal observational data collection as part of the XYZ Registry and are treated with a combination of Drug A and Drug B compared to controls who are treated with standard care for a period of a maximum of 2 years (or 4 years). Comparator patients will be included retrospectively as well prospectively. |
| --- | --- |
| **Hypothesis:** | Overall survival will be improved with Drug A and Drug B compared to standard of care. |
| **Population *(mention key inclusion-exclusion criteria):*** | Patients with biomarker Y+ positive metastatic [organ] cancer who progressed after at least of one line of treatment |
| **Exposure:** | Initiation of Drug A in combination with Drug B |
| **Comparator:** | Standard of care. In [anonymous country], SoC second line therapy is Drug C or in third line the SoC is Drug D. There will be 2 comparator arms. One will be initiation of Drug C or Drug D using concurrent years of data with the exposure arm. The other comparator group will be initiatiors of Drug C or Drug D using historical controls from years of data prior to availability of Drug A/B. |
| **Outcome:** | Overall Survival (OS) |
| **Time *(when follow up begins and ends):*** | Follow up from day after initiation of therapy until the first of outcome, discontinuation, add/switch therapy, disenrollment, end of study period, nursing home admission, death, progression of therapy, others to be discussed. |
| **Setting:** | Outpatient care |
| **Main measure of effect:** | Hazard Ratio (to be discussed). |

1. **Secondary objective 1 and research question**

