#### 7.4.3 Context and rationale for follow up

For the primary outcome of death and secondary outcomes of progression free survival and toxic adverse side effects, we will implement an on-treatment follow up analysis with censoring as defined in table 6. For health-related quality of life outcomes, we will use panel measurements in accordance with the XYZ registry’s data collection schedule. Details of the analyses for health-related quality of life outcomes will be determined after further discussion.

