#### Table 8. Operational Definitions of Follow Up

|  |  |  |  |
| --- | --- | --- | --- |
| **Follow up start** | Day 1 |  |  |
| **Follow up end^1^** | **Select all that apply** |  | **Specify** |
| **Date of outcome** | Yes |  | See Table 5 |
| **Date of death** | Yes |  | Discharged dead or registry recorded death, whichever came 1st |
| **End of observation in data** | Yes |  | Allow 30 day gaps in enrolment |
| **Day X following index date**  *(specify day)* | Yes |  | Day 365 |
| **End of study period**  (specify date) | Yes |  | 30-Sep-15 |
| **End of exposure**  *(specify operational details,*  *e.g. stockpiling algorithm, grace period)* | Yes |  | **Stockpiling algorithm:** If refill occurs before end of days supply, count overlapping days at the end of the subsequent dispensing’s day supply.  **Grace period:** Bridge gaps of ≤30 days between dispensation + days supply and refill. Add 30 days to last dispensation + days supply in a treatment episode. |
| **Date of add to/switch from exposure**  *(specify algorithm)* | Yes |  | Date that patient in exposed group is dispensed comparator drug or vice versa |
| **Other date** *(specify)* | Yes |  | Nursing home admission |

^1^ Follow up ends at the first occurrence of any of the selected criteria that end follow up.

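### Table 6 captures Drug A/B exposure in hospital only but standard-of-care exposure in hospital and palliative care, without a reason, which can bias overall survival toward Drug A/B

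*Protocol*

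**What the plan says.** Protocol Table 6 defines how exposure is captured from day 1 to censoring. The window, care setting and code type for Drug A/B read "1, censor] | Hospital | ATCC". For both the concurrent and the historical comparator they read "1, censor] | Hospital, palliative care | ATCC", so the care setting there is "Hospital, palliative care". Neither section 7.4.1 nor the algorithm for duration of exposure explains the difference.

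Other parts of the protocol bear on the same point:

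- Table 2 gives the setting as "Outpatient care" for the primary objective and for each secondary objective, in all arms.
- Table 3, which sets time 0, enters n/a for care setting in all three groups: "Date of incident dispensation of Drug A/B (time 0) | Single | Incident | [-∞, 0] | n/a | ATCC" for the exposed group and "Date of incident dispensation of standard care (time 0) | Single | Incident | [-∞, 0] | n/a | ATCC" for SoC.
- Section 7.4.3 says of death, progression-free survival and toxicity that "we will implement an on-treatment follow up analysis with censoring as defined in table 6".
- Table 8 ends exposure by dispensing, with the same tail in every arm: "Add 30 days to last dispensation + days supply in a treatment episode".
- Table 10 names Drug A/B against comparator 1 (concurrent) as the primary contrast.

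**The concern.** In an active-comparator cohort, both arms should be observed through the same window. Here the setting in which a dispensing counts depends on the arm. Patients dispensed anticancer drugs in palliative care are plausibly closer to death than those dispensed in hospital. A rule that recognises such dispensings for SoC only can add high-risk person-time and deaths to the comparator, or remove them from Drug A/B. Either makes Drug A/B look better on the primary outcome.

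The protocol marks its open items as to be discussed. These cells carry no such mark: they are filled in, and differ by arm. The results may inform reimbursement, so an artefact in this direction would matter.

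**Working it through.** **Step 1. How the asymmetry acts.**

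| Place in protocol | Drug A/B | SoC (both comparators) |
|---|---|---|
| Table 2, setting | outpatient | outpatient |
| Table 3, care setting at time 0 | n/a | n/a |
| Table 6, care setting from day 1 to censoring | hospital | hospital, palliative care |
| Table 8, end of exposure | last supply + 30 days | last supply + 30 days |

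*Follow-up route.* Table 8 counts dispensings, and Table 6 says which dispensings count. Take two patients whose drug goes on being dispensed after a move to palliative care. The SoC patient's refills are seen, so follow-up continues and a later death is an event. The Drug A/B patient's refills are not seen, so follow-up ends at the last hospital supply plus 30 days and a later death is lost. This holds even if section 7.4.3 meant to cite Table 8 rather than Table 6, because Table 8 depends on the dispensings that Table 6 admits.

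*Entry route.* If the Table 6 setting is also applied when initiators are selected, palliative-care starters of Drug C or D are captured and palliative-care starters of Drug A/B are not.

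**Step 2. The plan's own figure.** Inputs from the section on study size and feasibility: 5,000 exposed, 1:1 matching, 35% deaths in one year, HR 0.90. The two-sided 5% level is inferred from the 95% interval in Table 10.

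- Events: 10,000 × 0.35 = 3,500.
- Power (Schoenfeld) = Φ(|ln 0.90| × √(3,500/4) − 1.96) = Φ(0.1054 × 29.58 − 1.96) = Φ(1.157) = 87.6%.
- If 35% applies to SoC only, the exposed risk is 1 − 0.65^0.9 = 32.1%, events are 3,357 and power is 86.3%.

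The stated power of more than 80% is reproduced, and it does not depend on Table 6.

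**Step 3. Illustration of the entry route.** The protocol gives neither the share f of SoC patients dispensed in palliative care nor their hazard multiple m, so both are assumed. The true HR is set to 1.0.

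- Hospital hazard: λ = −ln(0.65) = 0.4308 per year.
- Drug A/B survival: S₁(t) = exp(−λt).
- SoC survival: S₀(t) = (1 − f)exp(−λt) + f·exp(−λmt).
- With event densities f₁ and f₀, the apparent HR θ solves the large-sample Cox score equation ∫₀¹ [f₁ − (f₁ + f₀)·θS₁/(θS₁ + S₀)] dt = 0, with administrative censoring at one year.

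| Share of SoC (f) | Hazard multiple (m) | Apparent HR |
|---|---|---|
| any | 1 | 1.00 |
| 2% | 2 | 0.98 |
| 5% | 2 | 0.96 |
| 5% | 3 | 0.93 |
| 10% | 2 | 0.92 |
| 10% | 3 | 0.88 |
| 10% | 5 | 0.83 |
| 15% | 5 | about 0.75 (0.755) |

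**Step 4. Could a bias of this size pass as a finding?** With 3,500 events the standard error of the log HR is √(4/3,500) = 0.0338, so an estimate below exp(−1.96 × 0.0338) = 0.936 is significant. At 10% and m = 2, the SoC one-year risk is 1 − (0.90 × 0.65 + 0.10 × 0.65²) = 37.3%. Events are 5,000 × (0.35 + 0.3727), about 3,614. The chance of a falsely significant benefit is Φ(|ln 0.9226| × √(3,614/4) − 1.96) = Φ(0.462) = 68%. At 5% and m = 2 (HR 0.960, 3,557 events) it is 23%.

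The follow-up route was not quantified. It would need the rate of moves to palliative care with drug continuing, on which the protocol is silent.

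**The case against.** A reader might infer that end-of-life patients and their deaths fall in the SoC arms alone. The text does not support that. Table 8 takes death from hospital discharge or registry records in all arms, and end-of-life patients treated in hospital count under Drug A/B.

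Nor does the text show that a palliative-care starter is barred from the exposed arm. Table 3 sets entry without a setting, and the Table 6 window opens on day 1, after entry. The entry route is conditional on Table 6 also being applied at selection.

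The follow-up route is narrower than it may look. No passage says that moving to palliative care ends exposure. A patient who stops drug on that move is handled alike in both arms, and deaths within days supply plus 30 days still count for Drug A/B. The limitations section acknowledges informative censoring and promises sensitivity analyses by reason for censoring and with censoring weights.

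The covariate list is also still open. If care setting at time 0 entered the propensity score, caliper matching would tend to drop SoC starters with no Drug A/B counterpart. It would be too strong to say that adjustment cannot help.

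Finally, n/a in Table 3 means not applicable, so it is not a third competing setting. The direct clash is between Tables 2 and 6.

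All of this stands, and it limits the claim. It does not explain why the arms differ in Table 6 or remove the effect on follow-up. Table 11 does not yet specify any sensitivity analysis, and censoring weights would not address differential entry.

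**Conclusion.** The point holds in limited form. Table 6 applies different care settings by arm, without rationale, in the primary contrast. It conflicts with the outpatient setting in Table 2 and adds a restriction that Table 3 does not impose at time 0. Applied as written, it can retain palliative-care patients in SoC longer than in Drug A/B. If it also governs entry, it can select them into SoC only. Both routes bias overall survival toward Drug A/B, provided that patients dispensed in palliative care have higher mortality. The covariates named so far do not address either route.

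The size is not known. The apparent HRs rest wholly on assumed shares and hazards, cover the entry route only and ignore matching. They run from no bias, through a trivial one (0.98), to one larger than the target effect (about 0.75). A reader might conclude that the artefact equals the HR of 0.90 for which the study is powered. That is possible under moderate assumptions (0.92 to 0.88 at a 10% share and two to three times the hazard), but the protocol does not demonstrate it.

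**What to change.** In Table 6, use one identical care-setting definition for Drug A/B and both comparators, and state that it applies both at time 0 and to ongoing exposure. Bring the Table 2 setting and the Table 3 care-setting column into line with it. If palliative care is kept as a capture setting, keep it for all three groups and include care setting at time 0 in the propensity score. Correct the cross-reference in section 7.4.3 so that it points to the table holding the censoring rules (Table 8).

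The cost is small: one column in two tables, the setting line in Table 2 and a cross-reference, all before data lock. If palliative-care dispensings are removed, there will be slightly fewer comparators. The power statement is unaffected as long as the 1:1 match can still be filled.

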#### 7.4.2 Context and rationale for outcome(s) of interest

Overall survival is the primary outcome of interest. This is a hard outcome that is of great interest to patients, clinicians and policy decision makers. We will explore secondary outcomes such as progression free survival, health related quality of life, toxic adverse effects, and healthcare resource utilization.

#### Table 7. Operational Definitions of Outcome

| **Outcome name** | **Details** | **Primary outcome?** | **Type of outcome** | **Washout window** | **Care Settings¹** | **Code Type^2^** | **Diagnosis Position^3^** | **Applied to study populations:** | **Outcome measurement characteristics/**  **validation** | **Source of algorithm** |
| --- | --- | --- | --- | --- | --- | --- | --- | --- | --- | --- |
| Overall Survival |  | Yes | Time-to-event | n/a | n/a | n/a | n/a | Exposure, comparator 1, comparator 2 | The positive predictive value of death in XYZ Registry is 96%. Sensitivity is 93%. | Hospital records + registry validation |
| Progression-free survival |  | No | Time-to-event | n/a | n/a | n/a | n/a | Exposure, comparator 1, comparator 2 | Unknown | (still in discussion) Derive variable from hospital pharmacy data + lab/report/imaging + toxic side effects + time to treatment failure |
| HRQoL (generic) |  | No | Continuous, categorical, binary | n/a | n/a | n/a | n/a | Exposure, comparator 1, comparator 2 | EQ-5D-5L is a validated instrument widely used in oncology (Schwenkglenks 2016 Expert Review of Pharmacoeconomics and Outcomes Research) | EQ-5D-5L |
| HRQoL (disease-specific) |  | No | Continuous, categorical, binary | n/a | n/a | n/a | n/a | Exposure, comparator 1, comparator 2 | EORTC-CXX and EORTC-CXY are validated widely used instruments ([name] 2021, European Journal of Cancer) | EORTC-CXX and EORTC-CXY |
| Toxic side effects |  | No | Time-to-event | n/a | n/a | n/a | To be discussed | Exposure, comparator 1, comparator 2 | To be discussed | To be discussed |
| Resource use |  | No | To be discussed | n/a | n/a | n/a | n/a | Exposure, comparator 1, comparator 2 | To be discussed | To be discussed |

^1^ IP = inpatient, OP = outpatient, ED = emergency department, OT = other, n/a = not applicable

^2^ See appendix for listing of clinical codes for each study parameter

^3^ Specify whether a diagnosis code is required to be in the primary position (main reason for encounter)

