| **Objective:** | To compare progression-free survival (PFS) and/or time to treatment failure (TTTF) in patients > 18 years with metastatic [organ] carcinoma with a biomarker Y+ mutation who have shown progression after first line treatment and have indicated informed consent for longitudinal observational data collection as part of the XYZ Registry and are treated with a combination of Drug A/B compared to patients who are treated with standard care for a period of a maximum of 2 years (or 4 years). Comparator patients will be included retrospectively as well prospectively |
| --- | --- |
| **Hypothesis:** | Progression-free survival (PFS) and/or time to treatment failure (TTTF) will be improved with Drug A and Drug B compared to standard of care. |
| **Population *(mention key inclusion-exclusion criteria):*** | Patients with biomarker Y+ positive metastatic [organ] cancer who progressed after at least of one line of treatment |
| **Exposure:** | Initiation of Drug A in combination with Drug B |
| **Comparator:** | Standard of care. In [anonymous country], SoC second line therapy is Drug C or in third line the SoC is Drug D. There will be 2 comparator arms. One will be initiation of Drug C or Drug D using concurrent years of data with the exposure arm. The other comparator group will be initiatiors of Drug C or Drug D using historical controls from years of data prior to availability of Drug A/B. |
| **Outcome:** | Progression-free survival (PFS) and/or time to treatment failure (TTTF) |
| **Time *(when follow up begins and ends):*** | Follow up from day after initiation of therapy until the first of outcome, discontinuation, add/switch therapy, disenrollment, end of study period, nursing home admission, death, progression of therapy, others to be discussed. |
| **Setting:** | Outpatient care |
| **Main measure of effect:** | Hazard Ratio (to be discussed). |

1. **Secondary objective 3 and research question**

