| **Population *(mention key inclusion-exclusion criteria):*** | Patients with biomarker Y+ positive metastatic [organ] cancer who progressed after at least of one line of treatment |
| **Exposure:** | Initiation of Drug A in combination with Drug B |
| **Comparator:** | Standard of care. In [anonymous country], SoC second line therapy is Drug C or in third line the SoC is Drug D. There will be 2 comparator arms. One will be initiation of Drug C or Drug D using concurrent years of data with the exposure arm. The other comparator group will be initiatiors of Drug C or Drug D using historical controls from years of data prior to availability of Drug A/B. |
| **Outcome:** | Resource utilization |
| **Time:** | Follow up from day after initiation of therapy until the first of outcome, discontinuation, add/switch therapy, disenrollment, end of study period, nursing home admission, death, progression of therapy, others to be discussed. |
| **Setting:** | Outpatient care |
| **Main measure of effect:** | Descriptive statistics (to be discussed) |

1. Research methods
   1. Study design

**Research design (e.g. cohort, case-control, etc.):** New user active comparator cohort study

**Rationale for study design choice:** In order compare the new treatment (Drug A/B) with standard of care (SoC), patients need to be followed from start treatment until censoring (death, progression, treatment failure, end of follow-up). Use of this design will help prevent time related biases such as depletion of susceptible, immortal time bias and adjustment for causal intermediates.

- 1. Study design diagram

[figure not shown]

- 1. Setting

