#### Table 10. Primary, secondary, and subgroup analysis specification

1. **Primary analysis**

| **Hypothesis:** | Exposure to Drug A/B increases risk of death relative to SoC comparators with the lower bound of the 95% confidence interval for the hazard ratio above 1.0. |
| --- | --- |
| **Exposure contrast:** | Exposure, comparator 1 (concurrent) |
| **Outcome:** | Death |
| **Analytic software:** | SAS 9.4: PHREG, PROC LOGISTIC, Pharmacoepi Toolbox nearest neighbor matching macro (http://www.drugepi.org/dope-downloads/) |
| **Model(s):**  ***(provide details or code)*** | *Outcome model:* Cox proportional hazards  followuptime*status(0) = exposure  *Propensity score model*: logistic regression  Exposure = Risk factors to be determined |
| **Confounding adjustment method** | ***Name method and provide relevant details, e.g. bivariate, multivariable, propensity score matching (specify matching algorithm ratio and caliper), propensity score weighting (specify weight formula, trimming, truncation), propensity score stratification (specify strata definition), other.*** |
|  | We will use logistic regression to estimate a propensity score using covariates that will be determined and recorded in an updated protocol before conducting inferential analysis. We will use this propensity score to nearest-neighbor match with a caliper of 0.2 standard deviations on the logit scale of the propensity score using the nearest neighbor algorithm from the Pharmacoepi Toolbox. |
| **Missing data methods** | ***Name method and provide relevant details, e.g. missing indicators, complete case, last value carried forward, multiple imputation (specify model/variables), other.*** |
|  | Patients with missing or unknown sex will be excluded. Multiple imputation will be used to impute missing data on health related quality of life at baseline. We assume that if no relevant claims diagnoses/procedures are present in the registry data, that the patient does not have the condition/procedure. |
| **Subgroup Analyses** | ***List all subgroups*** |
|  | 1. 2^nd^ vs 3^rd^ line of therapy |

1. **Secondary Analysis 1**

| **Hypothesis:** | Exposure to Drug A/B increases risk of progression free survival relative to SoC comparators with the lower bound of the 95% confidence interval for the hazard ratio above 1.0. |
| --- | --- |
| **Exposure contrast:** | Exposure, comparator 1 (concurrent) |
| **Outcome:** | Progression free survival |

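### The provisional PFS derivation mixes in toxicity and treatment failure, and the protocol does not say whether death, stopping and switching are PFS events or censoring

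*Protocol*

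**What the plan says.** - **Table 7, PFS row.** The details cell is empty and validation is unknown. The cell for the source of the algorithm is marked as still under discussion and reads "Derive variable from hospital pharmacy data + lab/report/imaging + toxic side effects + time to treatment failure". The entry is therefore provisional. It gives no rule for combining the parts and does not name death.
- **Table 2, Secondary objective 1.** The hypothesis is "Progression-free survival (PFS) and/or time to treatment failure (TTTF) will be improved with Drug A and Drug B compared to standard of care". Table 7 has rows for PFS and for toxic side effects, but none for TTTF.
- **Section 7.1.** "patients need to be followed from start treatment until censoring (death, progression, treatment failure, end of follow-up".
- **Table 8.** Follow-up ends at the first of several dates. Death has a row separate from the outcome ("Discharged dead or registry recorded death, whichever came 1st"). End of exposure (last supply plus 30 days) and add/switch are further rows. Section 7.4.3 applies on-treatment follow-up to PFS, and the Time row of Table 2 also lists discontinuation, add/switch, death and progression next to the outcome.
- **Table 10, Secondary Analysis 1.** The Cox model, the matching caliper and a 95% confidence interval criterion are already set for PFS.

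**The concern.** PFS is normally read as time to tumour progression or death. Two things in the provisional derivation pull it away from that.

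First, treatment failure and toxicity can end treatment while the tumour is stable. If they feed the PFS variable, the hazard ratio partly measures tolerability and prescribing. It then overlaps with the separate toxicity outcome, and it can differ from 1 when the treatments have the same effect on the tumour.

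Second, if death is not an event, a patient who dies before documented progression is simply censored. The endpoint is then time to progression, which answers a different question.

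The follow-up rules add a conflict. Stopping and switching are ingredients of treatment failure, and so of the PFS event, but they are also dates at which on-treatment follow-up ends. Two programmers could code the same patient differently, and both would be following the protocol.

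**Working it through.** **1. The plan's own figure.** There is no event rate or power for PFS. The only power statement (section 7.9) is for death: about 5,000 exposed patients matched 1:1, 35% deaths, HR 0.90, power above 80%. Deaths = 10,000 × 0.35 = 3,500. With two-sided 0.05, z = (√3,500 / 2) × |ln 0.90| − 1.96 = 29.58 × 0.1054 − 1.96 = 1.16, so power is 87.6%. The statement is reproduced, but it does not bear on PFS.

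**2. One occurrence, several codings.**

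| Occurrence | Under the Table 7 inputs | Under Table 8 and the Table 2 Time row |
| --- | --- | --- |
| Stop for toxicity, tumour stable | Event if toxicity or treatment failure counts; not an event if coded toxicity is used to rule progression out | End of follow-up |
| Switch to the other arm's drug | Possibly a treatment failure, so an event | End of follow-up |
| Death without progression | Not named | End of follow-up, not stated to be a PFS event |

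The ruling-out reading is possible because Table 4 takes absence of toxicity as a sign of progression at entry. It does not remove the problem: Table 10 reads a missing code as absence of the condition, so an uncoded toxicity stop would then look like progression.

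**3. Bias if non-tumour stops count as events.** Assume constant hazards and the same progression hazard in both arms. Then apparent HR = (progression + stops on A/B) / (progression + stops on SoC). All rates are assumptions. With progression at 0.15 per month:

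- stops 0.02 vs 0.06: 0.17 / 0.21 = 0.81
- stops 0.06 vs 0.02: 0.21 / 0.17 = 1.24
- stops 0.03 vs 0.05: 0.18 / 0.20 = 0.90
- equal stops: 1.00

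**4. A second set of assumptions, on one-year risks.** Convert each risk p to a hazard −ln(1 − p). With 60% progression in both arms (0.916) and stops of 10% vs 20% (0.105 vs 0.223), HR = 1.022 / 1.139 = 0.90. With 40% and 80% progression, the same stops give 0.84 and 0.94. At 5,000 per arm and 60% progression, events are 5,000 × (1 − 0.4 × 0.9) = 3,200 and 5,000 × (1 − 0.4 × 0.8) = 3,400. SE = √(1/3,200 + 1/3,400) = 0.0246, so z is about 4.4 and the 95% interval excludes 1 in about 99% of studies. At that sample size a modest definitional bias would look conclusive.

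**5. Effect of leaving death out.** Suppose the progression HR is 1 and the HR for death before progression is 0.7. PFS including death has HR = (h_prog + 0.7 × h_death) / (h_prog + h_death). With one-year progression 40% and death 35%, this is (0.511 + 0.7 × 0.431) / (0.511 + 0.431) = 0.86. With 80% and 10%, it is (1.609 + 0.7 × 0.105) / (1.609 + 0.105) = 0.98. The version without death shows 1.00 in both cases. The omission therefore hides an effect here and does not create one.

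**The case against.** The strongest reply is that the entry is openly a draft. The row carries a still-under-discussion label, the title page says undecided points will be developed later, and the column names sources, not events. The overall survival row in that column does not name death either, so silence about death in the PFS cell is weak evidence that death is excluded. Section 7.1 may also use censoring loosely for end of follow-up.

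Much of this stands. It rules out saying that the protocol has adopted a wrong PFS definition. It does not answer the point in full, because the row is not blank: it proposes ingredients, and two of them do not belong in PFS. The rest of the document does not supply the missing event rule, and Table 1 gives the same date for completing draft 1 and for registering the protocol.

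A reader might infer more than the documents support:

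- **That Drug A/B is an oral or targeted combination whose tolerability differs from SoC by design.** The protocol does not say so, and its toxicity hypothesis is no difference.
- **That comparability with the pivotal trial's PFS is lost.** The protocol speaks only of relative effectiveness in that trial and does not say that PFS was measured.
- **That omitting death creates a false benefit.** Step 5 shows that it can mask one.
- **That HR 0.90 is a benchmark for PFS.** Section 7.9 uses it for death.

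**Conclusion.** The point holds as a correction to make before the PFS row is finalised. The listed inputs would let stops unrelated to the tumour count as PFS events, PFS and TTTF are not kept apart, and no part of the protocol makes death a PFS event or settles whether stopping and switching are events or censoring.

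The size depends on rates that the protocol does not give. Under the assumed monthly hazards, a true HR of 1.00 becomes 0.81 or 1.24 depending on which arm stops more. This is the worst case, in which every such stop is scored, and equal stop rates leave the ratio at 1.00. The missing role of death is a separate matter: it changes the estimand, and over the assumed ranges it hides a PFS hazard ratio of 0.86 to 0.98. The documents do not support a claim that a false PFS result will occur, or in which direction.

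**What to change.** - **Table 7, PFS row:** define PFS as time from time 0 to the first of documented progression (imaging or report) or death from any cause. Remove toxic side effects and TTTF from the derivation.
- **Table 7, new row:** give TTTF its own definition as a separate supportive outcome, with discontinuation and switch as events.
- **Table 2, Secondary objective 1:** replace the and/or wording with PFS as the secondary outcome and TTTF as the supportive one.
- **Section 7.1, the Table 2 Time rows and Table 8:** state for each endpoint which occurrences are events and which are censoring, so that the same stop or switch cannot be both.

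Most of the cost is wording, since the registry is described as holding health records, claims and death data. There are two downsides. Progression never documented by imaging or report is counted late, or only at death; the separate TTTF analysis gives some view of how much that matters. Section 7.6.1 also notes that free-text notes need language processing before some characteristics can be extracted, so ascertaining progression from reports may take some work beyond the text change.
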